# Isoniazid preventive therapy completion in children under 5 years old who are contacts of tuberculosis cases in Lima, Peru: study protocol for an open-label, cluster-randomized superiority trial

**DOI:** 10.1186/s13063-022-07062-6

**Published:** 2023-01-24

**Keywords:** Tuberculosis, Child, Preschool, Latent *M. tuberculosis*/prevention and control, Peru, Randomized controlled trial

## Abstract

**Background:**

Children < 5 years old in contact with TB cases are at high risk for developing severe and fatal forms of TB. Contact investigation, BCG vaccination, and isoniazid preventive therapy (IPT) are the most effective strategies to prevent TB among children. However, the implementation of IPT faces challenges at several stages of the cascade of care of TB infection among children, particularly those less than 5 years old. In Peru, a large proportion of children do not complete IPT, which highlights the need to design effective interventions that enhance preventive therapy adherence and completion. Although the body of evidence for such interventions has grown, interventions in medium TB incidence settings are lacking. This study aims to test the effectiveness, acceptability, and feasibility of an intervention package to increase information and motivation to complete IPT among children < 5 who have been prescribed IPT.

**Methods:**

An open-label, cluster-randomized superiority trial will be conducted in two districts in South Lima, Peru. Thirty health facilities will be randomized as clusters, 10 to the intervention and 20 to control (standard of care). We aim to recruit 10 children from different households in each cluster. Participants will be caretakers of children aged < 5 years old who initiated IPT. The intervention consists of educational material, and short message services (SMS) reminders and motivators. The primary outcomes will be the proportion of children who picked up > 90% of the 24 weeks of IPT (22 pick-ups) and the proportion of children who picked up the 24 weeks of IPT. The standard of care is a weekly pick-up with monthly check-ups in a health facility. Feasibility and acceptability of the intervention will be assessed through an interview with the caretaker.

**Discussion:**

Unfavorable outcomes of TB in young children, high effectiveness of IPT, and low rates of IPT completion highlight the need to enhance adherence and completion of IPT among children < 5 years old. Testing of a context-adapted intervention is needed to improve IPT completion rates and therefore TB prevention in young children.

**Trial registration:**

ClinicalTrials.gov NCT03881228. Registered on March 19, 2019.

**Supplementary Information:**

The online version contains supplementary material available at 10.1186/s13063-022-07062-6.

## Background

Children exposed to tuberculosis (TB) are at high risk for developing severe and fatal forms of TB, such as TB meningitis, which has a low probability of survival, and a high risk of neurological sequela [1, 2]. In 2020, an estimated 1 million children had TB (11% of the global burden) and 204,000 died (16% of the global burden) [3]. In a recent meta-analysis, the case-fatality ratio for children less than 5 years old was 43.6% [4], compared to 3.0% in adults [5].

To prevent TB in children we need to diagnose and treat adult TB, the main infectious source [6], vaccinate newborns with BCG to decrease the incidence of severe forms of pediatric TB [7], and provide tuberculosis preventive therapy (TPT) to children with latent TB infection (LTBI); the latter reduces TB risk by more than 60% [8–10]. Isoniazid preventive therapy (IPT) is the most widely implemented TPT in high and moderate incidence countries. Other effective regimens such as 3 months of weekly rifapentine plus isoniazid, a 3-month regimen of daily isoniazid plus rifampicin, or 4 months of daily rifampin, are not widely implemented yet. In 2020, 36 countries reported use of rifapentine-containing regimens for research purposes and in some specific populations [9]. IPT delivery faces challenges through the continuum of care, from ruling out active TB to maintaining adherence to a daily dose of isoniazid for 6 months [11]. In 2019, only 29% of household contacts aged less than 5 years received TPT and the number of people initiating TPT dropped from 3.6 to 2.8 million between 2019 and 2020, due to the COVID-19 pandemic [5]. TPT completion rates are not reported by TB programs. However, a systematic review found that approximately 20% of children starting TPT completed it, even in high-income countries[12]. In Peru, a review of national routine surveillance data found that only 22% of eligible children < 5 years old received a full course of IPT between 2015 and 2016 [13], which is consistent with studies in Lima [14, 15].

When evaluating why do children not complete TPT, a scoping review of 146 studies identified concerns about adverse effects, low income, stigma, and transport as barriers and found these factors to be associated with lower retention in care [16]. Conversely, caregiver education and shorter regimens facilitated the completion of TPT [16]. Health system aspects such as poor linkage to TB services, patient’s mistrust of the health system, and lack of commitment to shared responsibility on TPT adherence by providers impacted treatment initiation, adherence, and completion in both adults and children on TPT [12]. A mixed-methods systematic review of 37 studies in high TB incidence settings [17] found that lack of prioritization of pediatric TB prevention, healthcare workers’ knowledge of TB infection, and characteristics of index cases such as female sex and direct kinship with children determined success in completing the full continuum of care.

There is limited evidence on the effectiveness of interventions to improve adherence to and completion of IPT and other TPT, especially in high and moderate TB incidence settings [18, 19]. For every 10 intervention studies in high-income countries (HIC), there is one in low- or middle-income countries (LMIC) [16, 20]. Education, counseling, incentives (monetary and non-monetary) and cultural case management may be effective for IPT completion, but results vary by context and underlying reasons for poor adherence [20, 21]. Directly observed preventive treatment (DOPT) and cash incentives have been implemented, but not tested, to improve TPT completion in children [16]. Daily SMS reminders for TB treatment have not been found to increase adherence [22]. However, weekly SMS reminders have shown promising results for IPT completion and adherence. A community-based intervention to improve adherence to IPT tested in 10 health facilities in Lesotho included mentoring healthcare workers, house visits, IPT-related educational activities, weekly calls, and SMS and showed a higher yield of contacts and treatment completion in the intervention group (RR 1.38 95% CI 1.03–1.84; *p* = 0.03) [23, 24]. A non-randomized study in Lima, Peru of a multi-component intervention with daily SMS reminders showed 72% TPT completion among adult and child contacts [25]. Based on the limited evidence of interventions in medium incidence settings, we will conduct an open-label cluster-randomized superiority trial designed to test the effectiveness and implementation of an intervention package to increase information and motivation to complete IPT among children < 5 who have been prescribed IPT.

## Methods

We adhered to the Standard Protocol Items: Recommendations for Interventional Trials (SPIRIT) 2013 Statement. SPIRIT checklist can be found in Additional file 1: Appendix 1.

### Study setting

The study will be conducted in Villa Maria del Triunfo (VMT) and San Juan de Miraflores (SJM), two districts in South Lima, Peru with a population of 432,835 and 408,538 people, respectively (2019). SJM has twenty-five and VMT twenty-six primary health care facilities under the Ministry of Health with a TB clinic (ESN-PCT, for its acronym in Spanish), providing TB care and prevention services for people living within its jurisdiction. The study will be conducted in the 30 largest of these health facilities, which each have at least one TB case per month,

### Study participants

Eligible participants will be caretakers of children who are (1) < 5 years old, (2) a contact of a TB patient, and (3) have an isoniazid preventive treatment (IPT) prescription from the TB physician. We will exclude caretakers not interested in participating in the study, those who do not have a mobile phone or, since August 2020, a smartphone with internet access using WhatsApp.

### Outcome

The primary outcomes will be the difference in the proportion of children who complete > 90% of the 24 pick-up weeks of IPT (22 pick-ups) and the proportion of children who complete the 24 pick-up weeks of IPT in the intervention and control groups. This will be determined by counting the IPT dispensing dates registered in the back of the TB index case treatment card. A secondary outcome to compare the proportion of children with a urine test positive for isoniazid in a subgroup of both arms was canceled due to the adaptations necessitated by the COVID-19 pandemic.

### Intervention description

We developed the intervention package directed at caretakers and children based on preliminary data in the study population, and behavioral and communication theory. The intervention consists of educational material, SMS reminders, and non-monetary incentives.

#### Rationale for the intervention

The Information-Motivation-Behavioral skills model guided the development of the intervention package [26, 27]. This model hypothesizes that information and motivation increase the likelihood of a behavior goal to occur and also exerts an influence in the acquisition of the behavioral skills needed to conduct and sustain the behavior. Our intervention will target the six constructs of the Transtheoretical Model for behavior change of pre-contemplation, contemplation, preparation, action, maintenance, and termination [28]. We will personalize the risk and reach effective objectives by using narratives from respected persons. We hypothesize that behavior change will occur when the caretaker reads about the particularly high TB risk of a child with household TB exposure and the protective effect of IPT when taken daily for 6 months. We will give cues to action so that the caretaker organizes the pick-up and intake. Through weekly SMS reminders and non-monetary incentives (a children’s storybook; since Aug 2020, a video) we will sustain risk awareness and perception of benefits throughout the 24-week IPT course. A weekly children’s story provides a positive side to balance the fear and stigma that may occur when attending a TB clinic to pick up IPT and places the child as the center of the prevention effort taken by the caretaker. The delivery of the intervention will be done parallelly to the provision of the standard of care which will be further described below.

#### Description of intervention components

##### Educational material

Caretakers in the intervention arm will receive an educational booklet (since August 2020 a video) that delivers information on why the child needs to take IPT, the benefits of taking it, and the risk of not taking it (or taking it intermittently). Practical recommendations to give the medication daily to the child are also provided. We will use an active voice and include behavioral recommendations to use daily reminders such as setting a phone alarm, an explanation about why the recommendations are important, numbers to support the recommendations expressed in familiar terms, and an explanation of the nature of risk [29]. We also included two narratives with a portrait picture, one from a local TB physician and one from a TB nurse, both respected healthcare workers in the study districts. We followed the research-based CDC Clear Communication Index which scores educational materials based on the language used. The caretaker is encouraged to read the booklet and discuss it with family members.

##### SMS reminders

SMS reminders will be sent from a central server a day prior to the scheduled IPT pick-up date for participants in the intervention arm. If a caretaker misses the pick-up, he/she will receive an SMS the next day to encourage resuming IPT. If the caretaker does not come back, we will send up to two more follow-up SMS on days 7 and 14 of the missed visit. If the caretaker goes back after 14 days of having missed a weekly pick-up, we will register the interruption, give the missed chapters to the child, and resume the SMS reminders unless the participant withdraws from the study.

##### Children’s storybook

Caretakers will receive a weekly children’s chapter book or video. The story and pictures were developed by an experienced children’s author and illustrator, and tell the story of a character, his family and where they live.

##### Standard of care (SOC)

The Peruvian standard of care [30] indicates that TB nurses interview recently diagnosed TB cases so they list their household and close contacts, and invite them for a TB screening. Upon presentation to the health facility, the nurse asks about symptoms in adult contacts and requests a smear microscopy if cough is present. All contacts < 14 years old are evaluated by a physician, who may request a chest X-ray, a tuberculin skin test (TST), and smear microscopy if the child can produce sputum. If active TB is a possibility, the child may be referred to a pediatric lung health specialist at the hospital. If active TB is ruled out in the child, the index case has drug-sensitive TB and the child is < 5 years old, the child is prescribed IPT for 6 months. TB diagnostic tests and treatment and IPT are free of cost to patients. Caretakers are verbally counseled to come every week to pick up IPT and to give it daily to the child. The child should be seen once a month at the facility to observe the well-being of the child; if the caretaker observes abdominal pain, vomiting, or jaundice, they should bring the child immediately to the health facility. The staff encourages the caretaker to select an IPT pick-up day that he/she can attend regularly. Adverse events related to isoniazid are rare in children [31–33] and routine monitoring of liver enzymes is not recommended unless the child has malnutrition, preexisting liver disease, or concomitant use of other hepatotoxic drugs [34, 35]. In those cases, the child will be managed by a pediatrician at a referral hospital. Data on contacts are registered on the back of the index case treatment card. The sex, age, kinship, and tests are done to rule out TB are registered for all contacts, and IPT prescriptions and pick-ups are registered for children. There are no structured recommendations or guidance on what to do if a caretaker does not come back to pick up IPT. In practice, the nurse may speak to the index case or conduct a household visit to speak to the caretaker and persuade her/him to resume IPT.

### Study procedures

#### Recruitment

TB nurses will ask eligible participants if they are interested in participating, and those who accept will be approached by the research nurse, who will inform caretakers about the study; those who provide written consent will be enrolled.

#### Randomization

We will randomize 30 clusters — health facilities — 10 to the intervention and 20 to control. We aim to recruit 10 children from different households in each cluster. Twelve of the 48 health facilities were excluded from these classifications as they had less than 1 TB case notification per month. To randomize the 36 health facilities, we classified them into 11 groups: 10 groups of 3 health facilities and one group of six facilities based on the number of TB cases reported in 2018, and the number of children < 5 started on IPT in 2018 as registered in routine health information systems. The group with 6 health facilities had the smallest number of cases per year. To select 2 control facilities and 1 intervention facility, we randomly selected from the group with the highest burden (group 1) until reaching the 10 intervention and 20 control facilities. Only the group classification and not the name of the facility was visible during randomization. Random numbers were generated with the Excel formula Rand() next to each group for the 36 health facilities. A witness set the criteria to the assignment of health facilities from groups 1 to 10. After we completed the assignments, the names of the health facilities were unblinded and the list of intervention and control facilities was made public (Available at bit.ly/3FRTA01). There were three stand-by health facilities for both groups in case a replacement was needed.

Based on 2018 TB case notifications, in which each facility reported an average of 68 TB patients (index cases) per year, and each case has a mean of four household contacts, of which, on average one is < 5 years old and that ~ 10% of children would be non-eligible for IPT (Multidrug-resistant TB contact, contraindications to isoniazid, other) and that 30% of those eligible for IPT would not be started on it (as per our findings), we estimated that more than 150 children would be eligible for the study in 1 year.

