#### Power calculations

We expect to increase IPT completion from 30 to 70% with the intervention. A structured behavioral intervention that included self-monitoring and incentives to increase adherence to IPT among children increased IPT completion (OR 2.4, 95% CI 1.7–3.5) [36]. Our intervention will use incentives targeting children and two additional tools targeting the caretaker. Therefore, we expect to increase it by 3.5, the upper CI. In that scenario, the outcome would occur in 70% of the intervention arm. Considering an intra-cluster correlation coefficient of 0.38, we will need to recruit 8 children in each of the 30 clusters (10 intervention, 20 control), to be able to detect that difference with 80% power. Considering potential losses (e.g., children whose IPT is stopped for medical reasons), we will recruit 10 children per cluster. Therefore, we will enroll 100 children in the intervention clusters and 200 children in the control clusters. Sample size calculations were made in Stata v.12 (Stata Corp, 12.0, College Station, TX).

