### Data management and analysis

Data will be imported into Stata V16. We will compare the proportion of children who completed IPT in both groups with statistical tests for small groups in an intention-to-treat approach, including all enrolled participants in the denominators. We will also compare the median number of weekly IPT pick-ups. We will compare the characteristics of caretakers, index cases, and children of the intervention and control arm. Missing data will be reported in descriptive tables. Medians and interquartile ranges will be calculated for continuous variables and proportions for categorical variables. Despite randomization, there may be confounding present regarding the probability of completing IPT. Potential confounders include the index case characteristics (sex, age, smear status), child characteristics (sex, age, kinship to the index case), caretaker’s characteristics (sex, age, kinship to the child, and to the index case, occupation, and education) the socio-economic status of the family and the health facility. To determine an unconfounded estimate of the effect of the intervention in the proportion of children who completed IPT, we will test models with a multivariate backward regression analysis. A saturated model with variables associated with IPT completion in our preliminary findings (smear status and treatment outcome of the index case, kinship and TST result of the child [14] and other variables associated (*p* < 0.1) with the outcome in the bivariate analysis will be tested against a model with variables with the weakest associations eliminated one by one. We will analyze the timing of the drop-outs (caretakers not coming back to pick up IPT) with Cox regression and the factors associated to that timing with a multivariate Cox regression analysis. We will report the proportion of enrolled to those eligible overall for the intervention group as well as per health facility, and we will report the full cascade of IPT (evaluation, prescription, initiation, completion) for the intervention and control facilities during the study period. As the data for the outcomes are routinely collected, we will follow the REporting of Studies Conducted using the Observational Routinely Collected Health Data (RECORD) statement to report the study findings [37].

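### Facilities were randomised 1:2 within ten groups of three, but the stated analysis names neither the groups nor the variables behind them; if the groups predict completion, a cluster-level analysis without them is conservative

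*Protocol article*

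**What the plan says.** The Randomization section of the protocol article sets the allocation: "We will randomize 30 clusters — health facilities — 10 to the intervention and 20 to control". The facilities were first classified into "10 groups of 3 health facilities and one group of six facilities based on the number of TB cases reported in 2018", with the number of young children started on IPT in 2018 as the second criterion. Allocation was then made group by group: "To select 2 control facilities and 1 intervention facility, we randomly selected from the group with the highest burden (group 1"), and so on down to group 10. This is restricted randomisation in ten triplets, each with one intervention and two control facilities. The same section adds: "There were three stand-by health facilities for both groups in case a replacement was needed".

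The Data management and analysis section gives the comparison: "We will compare the proportion of children who completed IPT in both groups with statistical tests for small groups", by intention to treat. It then lists potential confounders, describes a backward-elimination regression that starts from named variables plus any with p < 0.1 in bivariate analysis, and adds Cox models for the timing of drop-out. The health facility is on the confounder list. The randomisation groups, the 2018 TB case counts and the 2018 IPT starts appear nowhere in that section.

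**The concern.** Restricted randomisation balances the arms on the grouping factors. If those factors are related to the outcome, the true variance of the arm difference falls. An analysis that leaves them out still estimates the error from the full between-facility spread, so its standard error is too large. Its test then rejects less often than its nominal level, and its interval covers more than 95% of the time.

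This matters here because there are only 30 facilities and the assumed ICC is high. Most of the uncertainty lies between facilities, which is the part the grouping might explain.

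The covariate rule adds to the problem. Under it, a design variable could enter only by passing a bivariate p-value screen, and could then be eliminated. Listing the health facility as a confounder does not help: allocation is by facility, so facility fixed effects are aliased with arm. A facility random effect would handle clustering but would leave the variance due to the groups in the error.

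**Working it through.** **Inputs from the article.** Completion: "We expect to increase IPT completion from 30 to 70% with the intervention". Correlation: "Considering an intra-cluster correlation coefficient of 0.38". Size: "we will need to recruit 8 children in each of the 30 clusters (10 intervention, 20 control"), raised to 10 per cluster for losses. Alpha is not stated with the calculation; I assume 0.05 two-sided. The share *s* of between-facility variance explained by the groups is not in the document, so I vary it.

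**The plan's own figure.** For 70% vs 30%, 1:2 allocation, 80% power and continuity correction, the individually randomised size is 21 + 42. The design effect at 8 per cluster is 1 + 7 × 0.38 = 3.66. Then 21 × 3.66 = 76.9 and 42 × 3.66 = 153.7. Dividing by 8 gives 9.6 and 19.2, so 10 + 20 facilities. The stated design reproduces. The powers below are higher than 80% mainly because they use no continuity correction.

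**Share of variance between facilities.** For a facility mean this is 0.38 / (0.38 + 0.62/m): 0.83 at m = 8 and 0.86 at m = 10.

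**Cluster-level comparison.** With p(1 − p) = 0.21:
- Variance of a facility mean at m = 8: T = 0.21 × (0.38 + 0.62/8) = 0.0961.
- Group variance: G = s × 0.38 × 0.21. Within-group variance: W = T − G.
- True standard error of the arm difference: √[W × (1/10 + 1/20)] = √(0.15 W), because the groups are balanced across arms.
- With groups: 30 − 10 − 1 = 19 df, t = 2.093, variance estimate W.
- Without groups: 28 df, t = 2.048, expected variance estimate (9T + 19W + 18G)/28, which stays close to T.

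Example at s = 0.30: G = 0.0239 and W = 0.0721, so the true standard error is √(0.15 × 0.0721) = 0.104. The analysis without groups uses √(0.15 × 0.0952) = 0.1195. Half-widths are 2.048 × 0.1195 = 0.245 and 2.093 × 0.104 = 0.218, a ratio of 1.12.

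Results at 8 per cluster and 30% vs 70% (power from the non-central t):

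| Share s | Half-width without / with groups | Power without / with | Type I error without |
|---|---|---|---|
| 0% | 0.246 / 0.251 | 89.5% / 88.5% | 5.0% |
| 10% | 0.246 / 0.241 | 90.5% / 91.0% | 4.2% |
| 15% | 0.245 / 0.235 | 91.0% / 92.2% | 3.8% |
| 30% | 0.245 / 0.218 | 92.6% / 95.4% | 2.6% |
| 50% | 0.244 / 0.192 | 94.8% / 98.5% | 1.3% |

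The half-widths are equal at a share of about 5%. Below that, the 9 degrees of freedom spent on groups cost more than they return. A simulation with normal facility means agreed with these figures.

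**A 30-point difference.** The Power calculations section justifies 70% by an odds ratio of 3.5. Applied to 30%: odds 0.30/0.70 = 0.429; 0.429 × 3.5 = 1.5; 1.5/2.5 = 60%. Power without / with groups is then:
- 8 per cluster, variance 0.21: 67.5% / 66.0% at s = 0; 68.7% / 71.7% at 15%; 70.1% / 78.1% at 30%.
- 10 per cluster, variance 0.24 (that of a 60% proportion): 63% / 62%; 64% / 68%; 65% / 74% to 75%.

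The gain is about 3 to 9 points for shares of 15 to 30%, and the loss at s = 0 is about 1.5 points.

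**The case against.** The strongest objection is that this is silence and not error. The article never says that the groups will be left out, its small-group test is unnamed, and an analysis plan not shown may supply the term. That stands to this extent: one can say only that the analysis section does not mention the groups. It does not dispose of the point, because the section does fix a covariate list and a selection rule, and a design factor should not depend on that rule.

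A reader might infer that the trial will certainly lose power. The document does not support this. The groups were formed on counts of cases and treatment starts, not on completion, and no figure links the two. Below a share of about 5%, using the groups loses slightly.

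A reader might also infer that the trial's intervals will be too wide. That presumes a cluster-level analysis, which the article does not state. If children were compared individually with no allowance for clustering, the error would run the other way: at 8 per cluster the half-width would be 1.96 × √(0.21/80 + 0.21/160) = 0.123 instead of 0.246, and the type I error 2 × [1 − Φ(1.96/√3.66)], about 31%. That is a separate and larger matter. The question of the groups remains once clustering is handled.

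Finally, a cluster-level test without groups is valid, at worst conservative, and at the planned effect its power stays above 80% throughout. That is correct and limits the weight of the point.

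**Conclusion.** The point holds as a conditional matter of efficiency. The allocation was made within ten triplets, and the stated analysis does not secure any use of them. In an analysis that respects clustering, the consequence at the planned 40-point difference is a gain forgone of about 1 to 3 power points for shares of 15 to 30%, with intervals about 4 to 12% wider than needed. If the true difference is 30 points, as the article's own odds ratio implies, the gain forgone is about 3 to 9 points, in a setting where power without the groups is below 80%. If the groups are unrelated to completion, nothing is lost by leaving them out.

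These figures rest on two-sided alpha of 0.05, equal cluster sizes, an ICC of 0.38, approximately normal facility means and an assumed range for the groups' explanatory share. There is no bias and no inflated false-positive risk from this source.

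**What to change.** In Data management and analysis, make the primary comparison a facility-level analysis that respects the ten randomisation groups. One option is a permutation test that reassigns one intervention facility within each triplet (3^10 = 59,049 allocations). The alternative, which spends fewer degrees of freedom, is a model that allows for clustering by facility with 2018 TB cases and 2018 IPT starts as fixed covariates. Choose one before outcome data are examined, and exempt these terms from backward elimination.

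Also state how a stand-by facility that replaces another is assigned to a group. The 36 − 30 = 6 remaining facilities lie outside the ten triplets, so any replacement alters a triplet and the permutation set no longer matches the facilities analysed.

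The cost is wording: the 2018 data were used to randomise and are in hand. The statistical price is about 1 to 2 points of power if the groups turn out to be unrelated to completion.
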